## Abstract

**Background:** Incidence and mortality from cervical cancer have remained high due to many obstacles facing the implementation of organized screening programs in resource-constrained countries such as Nigeria. The application of mobile technologies (mHealth) to health services delivery has the potential to reduce inequalities, empower patients to control their health, and improve the cost-effectiveness of health care delivery.

**Aim:** To assess the efficacy of mobile technology intervention on Pap test screening adherence compared to a control condition and also determine the factors affecting the uptake of Pap smear screening practices among women in Lagos.

**Methods:** This is a multi-center randomized controlled trial that will involve women aged 25 to 65 years attending the General Outpatient clinics of the two tertiary health institutions in Lagos, Nigeria between April and December 2020. At baseline, a total of 200 National Health Insurance Scheme (NHIS) enrollees will be randomized to either a text message arm or usual care (control) arm. The primary outcome is the completion of a Pap smear within 6 months of enrolment in the study. The associations between any two groups of continuous variables will be tested using the independent sample t-test (normal distribution) or the Mann-Whitney U test (skewed data) and that of two groups of categorical variables with Chi-square
*X
^2^*or Fisher's exact test where appropriate. Using binary logistic regression model, we will adjust for age and other relevant sociodemographic and clinical variables and adherence to Pap test screening. Statistical significance will be defined as
*P*-value less than 0.05.

**Discussion: **The mHealth-Cervix study will evaluate the impact of mobile technologies on cervical cancer screening practices in Lagos, Nigeria as a way of contributing to the reduction in the wide disparities in cervical cancer incidence through early detection facilitated using health promotion to improve Pap smear screening adherence.

**Registration**:
PACTR202002753354517 13/02/2020

## Introduction

Cervical cancer is a major public health problem and is the fourth most common cancer in women worldwide accounting for an estimated 570,000 new cases annually
^1^. More than 80% of the global burden of cervical cancer occurs in the less developed regions, where it accounts for almost 12% of all female malignancies
^2,
3^. In 2018, an estimated 311,000 deaths were attributed to cervical cancer, which accounts for 7.5% of all female cancer deaths with 70% of these occurring in developing countries
^1^. Early detection of precursor lesions of cervical cancer through the use of screening tests has drastically reduced the incidence of the disease, especially in Western countries where Pap smear (cytology-based) screening has been introduced and now covers almost all eligible women
^4^. However, in resource-constrained countries of the world such as Nigeria, cervical cancer incidence and mortality have remained high due to the many obstacles facing the implementation of organized screening programs
^5^. A recent study conducted by our team among women in Lagos revealed Pap smear screening uptake of about 23% despite an awareness rate of 55%
^6^.

The use of mobile technologies has increased exponentially in the last few years
^7^. We reported in a study conducted in 2018 that mobile telephones could be found in 95% of households in Lagos and these were widely distributed across all socioeconomic classes
^8^. Because of this increased access to technologies, mobile health (mHealth), or “medical and public health practice involving the use of mobile devices”
^9^, has great potential in many health areas such as promotion and prevention
^10^. The World Health Organization (WHO) report on mHealth in 2011
^9^ states that mobile health strategies exist in at least 75% of the countries in WHO regions. The application of mHealth to health services delivery has the potential to reduce inequalities, empower patients to control their health, and improve the cost-effectiveness of health care delivery
^11^.

Although still limited, there is growing evidence of success in the use of mobile phones for health (mHealth technologies) to support cancer prevention
^12–
15^. Nevertheless, there is currently no reported randomized controlled trial in sub-Saharan Africa (sSA) that examines the use of mobile health technologies in cancer prevention. This study will, therefore, aim to ascertain the efficacy of an intervention using mobile technologies on Pap smear screening adherence compared to standard care; and also determine the factors affecting the uptake of Pap smear screening services among women in Lagos, Nigeria. The introduction of mHealth, now regarded as one of the most promising investments for health in developing countries
^16^, is a key innovative concept that will offer a unique opportunity for a paradigm shift in cervical cancer control in a resource-constrained setting like Nigeria and other parts of sSA.

## Protocol

### Study design

This study (mHealth-Cervix) is a multi-center randomized controlled trial that will involve women aged 25 to 65 years who are attending the General Outpatient (GOP) clinics of two public tertiary health institutions in Lagos, Nigeria – Lagos University Teaching Hospital (LUTH), Idi-Araba and Lagos State University Teaching Hospital (LASUTH), Ikeja between April and December 2020. The trial protocol has been registered in the Pan African Clinical Trial Registry (PACTR) (
PACTR202002753354517; version 3.0; February 13, 2020).

### Study settings

LUTH and LASUTH are the two foremost public tertiary health institutions in Lagos that offer speciality and sub-speciality care including gynaecological oncology services such as Papanicolaou (Pap) test, human papillomavirus (HPV) testing and colposcopy for cervical cancer screening. The GOP clinics of the two hospitals run from Monday to Friday each week and attendees at the clinics are mostly enrollees of the National Health Insurance Scheme (NHIS) who have free cervical cancer screening as part of their health coverage. The hospitals act mainly as referral centers for other government-owned and private hospitals in Lagos State. Lagos State is the commercial capital of Nigeria which has a population of over 9 million inhabitants.

### Study population and eligibility criteria

Eligible women are NHIS enrollees aged between 25 and 65 with no prior history of cervical cancer or cervical dysplasia; those not adherent with current recommendations for Pap smear screening (have not had a Pap smear within the last three years); those owning and using a personal cell-phone; those free from any mental or physical disabilities that inhibit them from understanding the implications of the study and those not considering relocating from their current residence within the next year. The exclusion criteria include women younger than 25 and older than 65 years old, those with history of cervical dysplasia and cancer, those who had a Pap test within the last three years, those with an ongoing pregnancy and those who refuse or withdraw consent during the study.

### Participants’ enrollment and data collection

Investigators will identify eligible women from the GOP clinics of the two study sites on each day of the study period after which a 20–30 minutes educational health talk on cervical cancer and its prevention is given to these women by the clinic midwives with the assistance of the clinics’ health care teams as part of their usual standard of care. Eligible women are then invited by the investigators to give consent for participation in the clinical trial upon explanation of the purpose and nature of the study. Once consent is obtained, an interviewer-administered questionnaire (see extended data
^17^) is then used to obtain baseline information on sociodemographic variables, cell-phone use, and distance of participants’ residence from the clinics (measured in kilometer using the Google maps). Each woman will receive an estimated $5 credit charge on their cellphones as a token to enable the investigators to keep their phone numbers for as long as the intervention lasts. The women in both arms are each given the complementary card containing the cell-phone number of the cytology clinic coordinators (who are also part of the study) and are subsequently scheduled for 6-month follow-up appointments from their dates of study enrolment. After follow-up, data will be collected from each woman on completion of Pap test screening, the number of GOP clinics attended, the interval from enrollment to date of Pap smear testing and functionality of cell-phone during the same follow-up period (that is, if the cell-phone was in use for at least 5 out the 6 months follow-up or not).

### Randomization

Following the baseline assessment, enrolled women will be randomized to either a text message (intervention) arm or usual care (control) arm using computer-generated block randomization codes using
Random Allocation software version 1.0 (May 2004) by a study statistician. Investigators and statisticians will be blinded to the allocation groups [
Figure 1]. The allocation sequence is concealed in sealed opaque envelopes that will be kept in a locked file cabinet at each of the study sites until participants assignment is completed.

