### Statistical methods

Sample size – We calculated sample size using
G*Power for Windows version 3.1.9.2 (Kiel University, Germany). Using data from our published study
^6^, we estimated the proportion of Pap smear adherence to be approximately 23% for the usual care (control) arm and 60% for the text message (intervention) arm. This is powered for a two-sided test with a Type I error rate of 5% and 80% power, i.e. Zα=1.96 and Zβ=0.84, adjusted for a 10% attrition rate. Therefore, the power calculations will be based on a sample size of 100 in each of the two study arms (making a total sample size of 200).

Statistical analysis – The intention-to-treat principle will be used in the final analyses. Statistical analyses will be carried out using
SPSS version 23.0 for Windows (Armonk, NY: IBM Corp.). Pap smear adherence will be coded as a binary variable. The intervention will be evaluated based only on Pap smear completion at 6-month after the enrollment and baseline survey. The associations between any two groups of continuous variables will be tested using the independent sample t-test (normal distribution) or the Mann-Whitney U test (skewed data) and that of two groups of categorical variables with Chi-square (
*χ*
^2^) or Fisher's exact test where appropriate. Using binary logistic regression analysis, we will adjust for age, socioeconomic class, parity, marital status, number of GOP clinic attendance, the distance of residence from the clinics, interval from enrollment to date of Pap smear testing, the functionality of cellphones and other relevant demographic and clinical variables. Statistical significance will be defined as
*P*-value less than 0.05.

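### The protocol does not say whether the block lists are separate for each hospital, and its named covariates omit hospital; settling both is a minor improvement that costs almost nothing

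*Protocol article*

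**What the plan says.** The Study design section enrols women from the "General Outpatient (GOP) clinics of two public tertiary health institutions in Lagos, Nigeria". The Randomization section specifies "computer-generated block randomization codes", produced by a study statistician, and sealed opaque envelopes "kept in a locked file cabinet at each of the study sites until participants assignment is completed". It gives no stratification factor and does not say whether there is one list or two.

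The Statistical methods section gives chi-square or Fisher tests for two-group comparisons of categorical variables. It then describes a logistic regression: "we will adjust for age, socioeconomic class, parity, marital status, number of GOP clinic attendance, the distance of residence from the clinics", followed by the interval to the smear, cell-phone functionality "and other relevant demographic and clinical variables". Hospital is not among the eight named covariates. The closing clause neither names it nor rules it out.

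**The concern.** The outcome is a completed smear, obtained through a hospital's own outpatient and cytology clinics, so uptake could differ between hospitals for reasons unrelated to the text messages. Two cases follow, and only one can apply.

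- **One list shared between the two cabinets.** Blocks balance the arms overall but need not balance them within a hospital.
- **A separate blocked list per hospital.** The arms are balanced within hospital, but an analysis without hospital overstates the standard error when the hospitals differ.

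In either case, having hospital in the analysis helps. There is also a point for the secondary endpoint, the factors affecting uptake. A model with distance from the clinics but without hospital can credit distance with what is really a difference between hospitals.

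**Working it through.** **Inputs from the protocol (Statistical methods).** Uptake "approximately 23% for the usual care (control) arm and 60% for the text message (intervention) arm"; two-sided 5%; 80% power; 10% attrition; 100 per arm, so 100 × 0.9 = 90 evaluable.

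**Assumptions.** The protocol gives neither the split of women between hospitals nor the difference in uptake. Splits of 90/90 and 130/50 evaluable women were tried, with gaps in control uptake of 0, 10, 20 and 30 points around 23% (with equal hospitals, 30 points means 38% against 8%). The odds ratio between hospitals is the same in both arms.

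**1. The plan's own sample size.** With mean rate 0.415:

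n = [1.96√(2 × 0.415 × 0.585) + 0.84√(0.23 × 0.77 + 0.60 × 0.40)]² / 0.37² = (1.366 + 0.542)² / 0.1369 ≈ 26.6, so 27 per arm, and 27/0.9 = 30 after attrition.

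The stated 100 is not reproduced, but it errs on the large side. Power at 90 per arm:

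- null SE = √(0.48555/90) = 0.0735
- alternative SE = √(0.4171/90) = 0.0681
- (0.37 − 1.96 × 0.0735)/0.0681 = 3.32, so power is 99.96%.

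**2. Balance if one list is shared** and hospital is unrelated to list order. The number of intervention women at a hospital of size n, out of 200 with 100 per arm, is hypergeometric with variance n × ¼ × (200 − n)/199.

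| Hospital sizes | SD of arm difference within hospital | P(difference ≥ 10) | P(difference ≥ 20) |
|---|---|---|---|
| 100/100 | 2√12.56 = 7.1 | 0.20 | 0.007 |
| 60/140 | 2√10.55 = 6.5 | 0.16 | 0.003 |

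A difference of 10 (55/45 at one hospital, 45/55 at the other) with a 30-point gap moves the crude risk difference by (0.55 − 0.45) × 0.30 = 0.03.

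**3. Power at the planned effect.** Simulation, 40,000 runs per scenario, crude chi-square against Cochran-Mantel-Haenszel (CMH) by hospital. Power is at least 99.9% in every scenario.

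**4. Power at an assumed 23% against 43%.** This is close to the smallest effect that 90 per arm detects with 80% power (23% against 42.5%).

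| Gap | Split | Shared list, chi-square | Shared list, CMH | Separate lists, chi-square | Separate lists, CMH |
|---|---|---|---|---|---|
| 0 | 90/90 | 82.5% | 82.3% | 82.1% | 82.1% |
| 10 | 90/90 | 82.1% | 82.5% | 82.7% | 83.1% |
| 20 | 90/90 | 82.1% | 84.6% | 82.7% | 84.4% |
| 30 | 90/90 | 82.3% | 88.3% | 84.8% | 88.6% |
| 30 | 130/50 | 82.4% | 85.7% | 83.4% | 86.2% |

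From shared list with chi-square to separate lists with CMH, the gain is nil with no gap. With equal hospitals it is 1.0 point at a 10-point gap, 2.3 at 20 and 6.3 at 30. With 130/50 it is 3.8 at 30. Simulation error is about √(0.82 × 0.18/40,000) = 0.2 points per entry. Nearly all the gain comes from the analysis: with CMH, shared and separate lists differ by 0.6 points at most. At a 30-point gap and equal hospitals, separate lists lower the SD of the crude risk difference from 0.068 to 0.062.

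**5. Type I error (23% in both arms).** Crude test, shared list: 4.8% to 5.1%. Crude test, separate lists: 4.3% at a 20-point gap and 3.5% at 30 points (equal hospitals). CMH: 4.9% to 5.2% throughout.

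**6. The odds ratio.** Take assumed control uptake of 10% and 45% at two equal, perfectly balanced hospitals, and an odds ratio of 2.2 at each (log 0.79). Intervention uptake is then 19.6% and 64.3%, with averages of 42.0% against 27.5%. The crude odds ratio is (0.420/0.580)/(0.275/0.725) = 1.91, log 0.65. Nothing is confounded here; the crude and within-hospital odds ratios are different quantities. The risk difference is 14.5 points either way.

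**The case against.** The strongest reply is that this is a condensed article. List structure is commonly left to the full protocol, and envelopes held at each hospital fit separate lists per hospital, which would be stratification in practice. That stands: a reader might infer an unstratified design, but the article is silent on the matter. It also does not designate an unadjusted primary test; it gives categorical tests in general terms and then an adjusted model.

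The covariate list is open-ended, so hospital is not excluded. This stands only in part. The article does not defer the analysis; it names eight covariates, and hospital of enrolment does not clearly fall under demographic or clinical variables.

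A reader might also infer that hospital is a strong predictor of uptake. The documents do not support this. Both sites are public tertiary hospitals in Lagos with cytology services, clinic attendees are mostly insured for free screening, and the health talk and follow-up are common to both. No uptake by hospital is given. A difference is plausible, but its size is unknown.

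Finally, chance imbalance by hospital is already covered by the error rate of the crude test, as step 5 confirms.

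**Conclusion.** The point holds as a minor improvement. The protocol leaves the list structure unstated and omits hospital from its named covariates. No result would be invalid for that reason, and no power is lost at the planned effect. The gain depends on two assumptions outside the protocol: a true effect well below the planned 37 points, and a real difference in uptake between hospitals. With a 20-point effect it is about 0 to 2 points of power for gaps up to 20 points, and about 6 points (82.3% to 88.6%) for a 30-point gap with equal hospitals. If the lists are already separate, the cost of ignoring hospital is a conservative test, at worst about 3.5% instead of 5% in the scenarios tried.

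Two stronger readings fail. Within-hospital imbalance and a conservative standard error do not add up, because they belong to different list structures. A crude odds ratio closer to 1 is not a biased one; step 6 shows the shift under perfect balance.

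**What to change.** - **Randomization:** generate one permuted-block list per hospital and say so in one sentence. If this is already the arrangement, only the sentence is needed.
- **Analysis:** add hospital as a fixed covariate in the logistic model. Report a Cochran-Mantel-Haenszel comparison stratified by hospital, with a stratified risk difference and 95% CI.

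The cost is two lists from the same software, one model term and a few lines of text. Study status reports that recruitment had not begun at submission, so both changes were then open. If enrolment has since started, the analysis change is still available before data are examined by arm, and it carries nearly all the gain in power.

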**Figure 1. f1:**
[figure not shown]
Trial flow chart.

*Intervention (mHealth) arm* – We chose
Nexmo® as the platform to deliver the mHealth messages given its low cost and reliability. Participants will be sent messages containing information and encouragement to undergo cervical cancer screening. Information will also be provided about the Cytology clinic hours, contact information and locations in the two participating hospitals. Information and motivational text messages will be delivered twice monthly for the next 6-months after enrollment.

*Usual care (control) arm* – Participants randomized to the control arm will not receive additional reminder messages from study staff other than the usual care received at enrollment. Usual care consists of any information on Pap tests and cervical cancer risk reduction typically provided by midwives to all women at the clinics as will be done at enrollment. These women can then schedule an appointment for their Pap smear testing in person at the GOP or Cytology clinics at any time during the 6-month follow-up period.

### Study endpoints

Primary endpoint – This is the completion of a Pap smear within 6 months of enrollment in the study. Participants will be tracked via medical record review as well as through phone calls at 6-month after their enrolment.

Secondary endpoint – This is an assessment of the various factors affecting Pap smear uptake or adherence within 6-month of enrollment among the participating women.

### Statistical methods

Sample size – We calculated sample size using
G*Power for Windows version 3.1.9.2 (Kiel University, Germany). Using data from our published study
^6^, we estimated the proportion of Pap smear adherence to be approximately 23% for the usual care (control) arm and 60% for the text message (intervention) arm. This is powered for a two-sided test with a Type I error rate of 5% and 80% power, i.e. Zα=1.96 and Zβ=0.84, adjusted for a 10% attrition rate. Therefore, the power calculations will be based on a sample size of 100 in each of the two study arms (making a total sample size of 200).

Statistical analysis – The intention-to-treat principle will be used in the final analyses. Statistical analyses will be carried out using
SPSS version 23.0 for Windows (Armonk, NY: IBM Corp.). Pap smear adherence will be coded as a binary variable. The intervention will be evaluated based only on Pap smear completion at 6-month after the enrollment and baseline survey. The associations between any two groups of continuous variables will be tested using the independent sample t-test (normal distribution) or the Mann-Whitney U test (skewed data) and that of two groups of categorical variables with Chi-square (
*χ*
^2^) or Fisher's exact test where appropriate. Using binary logistic regression analysis, we will adjust for age, socioeconomic class, parity, marital status, number of GOP clinic attendance, the distance of residence from the clinics, interval from enrollment to date of Pap smear testing, the functionality of cellphones and other relevant demographic and clinical variables. Statistical significance will be defined as
*P*-value less than 0.05.

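### The stated inputs require about 27 to 36 enrolled women per arm, not 100, so at least one of the sample size, the power and the target effect is misstated

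*Protocol article*

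**What the plan says.** The sample size paragraph under Statistical methods in the protocol article gives every input of a two-proportion calculation. It takes "the proportion of Pap smear adherence to be approximately 23% for the usual care (control) arm and 60% for the text message (intervention) arm". On the error rates it says: "This is powered for a two-sided test with a Type I error rate of 5% and 80% power", and it spells out the normal quantiles as "80% power, i.e. Zα=1.96 and Zβ=0.84". The result is described as "adjusted for a 10% attrition rate". The next sentence, introduced as a consequence of these inputs, is that "the power calculations will be based on a sample size of 100 in each of the two study arms", or 200 women in total.

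The primary endpoint (Study endpoints) is binary: a Pap smear completed within 6 months of enrolment. Categorical comparisons are to use the chi-square test or Fisher's exact test. The article gives no other basis for 100 per arm, such as a subgroup analysis, a clustering allowance, the secondary endpoint, the regression model or deliberate oversizing.

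**The concern.** A difference of 37 percentage points is very large for a binary outcome, and 80% power for it should need only a few dozen women per arm. A result of 100 per arm suggests that some figure in the paragraph is not the one used in the calculation.

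This paragraph is the only power justification for the primary endpoint. It tells readers, the ethics committee and the steering committee what effect the trial was built to detect and why 200 women are needed. If its figures do not agree, neither statement can be relied on, and the calculation cannot be reproduced in the CONSORT report that the article promises.

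**Working it through.** **Inputs, all from the sample size paragraph.** p1 = 0.23, p2 = 0.60, difference d = 0.37, Zα = 1.96, Zβ = 0.84, equal arms, 10% attrition. The mean proportion is (0.23 + 0.60)/2 = 0.415.

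**Step 1: try to reproduce 100 per arm.**

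Pooled formula: n = [Zα√(2 × 0.415 × 0.585) + Zβ√(0.23 × 0.77 + 0.60 × 0.40)]² / d²

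- First term: 1.96 × √0.48555 = 1.3658
- Second term: 0.84 × √0.4171 = 0.5425
- n = (1.9083)² / 0.1369 = 26.6, so 27 evaluable per arm
- With attrition: 27 / 0.9 = 30 enrolled per arm, 60 in total

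Unpooled formula: n = (1.96 + 0.84)² × 0.4171 / 0.1369 = 23.9, so 24 evaluable; 24 / 0.9 = 26.7, so 27 enrolled.

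Continuity-corrected: (26.6 / 4) × [1 + √(1 + 4 / (26.6 × 0.37))]² = 31.8, so 32 evaluable; 32 / 0.9 = 35.6, so 36 enrolled.

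Results per arm, two-sided 5%, 80% power:

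| Method | Evaluable | Enrolled |
|---|---|---|
| Unpooled | 24 | 27 |
| Pooled | 27 | 30 |
| Arcsine | 27 | 30 |
| Fisher's exact (power 0.800 at n = 31) | 31 | 35 |
| Continuity-corrected | 32 | 36 |

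The total is therefore 2 × 27 = 54 to 2 × 36 = 72.

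**Step 2: look for a variant that gives 100.** In each pair below, the first figure is the pooled formula and the second is continuity-corrected, both enrolled per arm.

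- One-sided 5%, 80% power: 24 and 29
- Two-sided, 90% power: 40 and 46
- Two-sided, 95% power: 49 and 55
- Two-sided, 99% power: 68 and 74

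Inflating by 1.1 instead of dividing by 0.9 changes these by at most one woman per arm. None comes near 100.

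**Step 3: power at the stated size for the stated effect.** Power = Φ{[d√n − 1.96√0.48555] / √0.4171}

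- n = 90 (100 less 10%): (0.37 × 9.487 − 1.3658) / 0.6458 = 3.32, so power is 0.9996
- n = 100: (3.70 − 1.3658) / 0.6458 = 3.61, so power is 0.9998

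**Step 4: effect detectable with 80% power at the stated size, control at 23%.** For 90 per arm, try p2 = 0.425, so that d = 0.195 and the mean proportion is 0.3275.

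- [0.195 × 9.487 − 1.96√(2 × 0.3275 × 0.6725)] / √(0.1771 + 0.2444) = (1.850 − 1.301) / 0.649 = 0.846, so power is 0.80

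The detectable intervention rate is thus about 42.5%, a difference of about 19.5 points. With all 100 per arm evaluable it is about 41.5%. With the continuity correction, 43% needs 96 evaluable per arm and 44% needs 88, so 90 per arm falls between the two.

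**The case against.** The strongest defence is that the error is on the safe side. The trial has more than enough women for its stated effect, and the primary comparison and its type I error rate are untouched. This stands. A reader might infer from a faulty calculation that the trial is underpowered, and for 23% v 60% the arithmetic shows the opposite.

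A reader might also infer that both the stated power and the stated target effect are wrong. The document does not support that. If 23% v 60% is the intended effect and 100 the intended size, only the power is misstated. If 80% power with 100 per arm is right, the target is misstated. If effect and power are both right, the size does not follow from them.

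Nor does the document support saying that a non-significant result would be misread. Such a result would be judged from the estimate and its confidence interval, not from the planning power.

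A separate reason for 200 women is conceivable. The planned logistic model names eight covariates and allows others, and factors affecting uptake form the secondary endpoint. At the assumed rates, 27 evaluable per arm would yield 27 × 0.23 + 27 × 0.60 = about 22 completions, while 90 per arm would yield 90 × 0.23 + 90 × 0.60 = about 75. But the article does not offer this reason. It presents 100 as the outcome of the two-proportion calculation.

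Finally, a journal article condenses a fuller protocol. That would excuse a missing detail. Here the inputs and the result are all printed, and they disagree.

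**Conclusion.** The point holds as an inconsistency between printed figures. The stated size is 200/72 = 2.8 to 200/54 = 3.7 times what the stated inputs require. If the 23% v 60% target and 80% power are both as intended, that is 128 to 146 women beyond the stated basis, with no reason given. Which of size, power and target effect is misstated cannot be settled from the document.

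The 42.5% rate is only what this sample size can detect with 80% power. The article nowhere calls it a target or describes a 19.5-point gain as meaningful, so it should not be presented as the planning assumption.

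The figures assume equal arms, independent outcomes between women, a control rate of 23% as stated, and attrition of exactly 10%. The choice of formula or attrition convention does not alter the conclusion. The consequence is for the reproducibility and accuracy of the design statement, not for the validity of the primary test.

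**What to change.** First check what was entered in G*Power. Then state one of two things: the inputs that actually produced 100 per arm, correcting the 60% or the 80% if either differs from what was entered; or the separate reason for choosing a larger size. In either case give the matching power.

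If 200 women and 23% v 60% are both kept, the statement could read: *100 per arm (90 evaluable after 10% attrition) gives over 99% power for 23% v 60%; the smallest difference detectable with 80% power at this size is 23% v about 42.5%.* The second clause should stay labelled as a detectable difference.

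The cost is one corrected sentence, plus a sentence of justification if the size was chosen on other grounds. No change in enrolment is needed. The Study status section says that recruitment had not begun at submission, so at that stage the correction could be made before any outcome data existed.

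### The arm-effect logistic model has too many covariates for about 58 to 75 events, and the plan names no effect measure on the proportion scale

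*Protocol article*

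**What the plan says.** The analysis paragraph of Statistical methods plans a binary logistic regression in which "we will adjust for age, socioeconomic class, parity, marital status, number of GOP clinic attendance, the distance of residence from the clinics". The list goes on to the time from enrolment to the smear and whether the phone was working, which makes eight named covariates. It ends "and other relevant demographic and clinical variables". No coding and no cap on the number of terms is given.

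The same paragraph codes adherence as binary, applies intention to treat, and compares groups by t-test or Mann-Whitney for continuous variables and by chi-square or Fisher's exact test for categorical ones. It names no risk difference, risk ratio or confidence interval.

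The sample size paragraph assumes adherence of "approximately 23% for the usual care (control) arm and 60% for the text message (intervention) arm", is "adjusted for a 10% attrition rate", and states that "the power calculations will be based on a sample size of 100 in each of the two study arms".

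The section on enrollment and data collection shows that three of the eight covariates are gathered after follow-up: clinic attendances, time to the smear, and phone functionality. The secondary endpoint is the set of factors that affect uptake.

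**The concern.** Maximum-likelihood odds ratios are biased away from 1 when a logistic model has few events per coefficient. The listed model is long, its end is open, and the trial is small. If the texts work, the adjusted odds ratio would on average overstate the effect and be less precise than one from a short model. Small categories, for example in marital status, can also produce separated coefficients, which would damage the factor odds ratios wanted for the secondary endpoint.

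A second and separate issue is scale. The trial was sized on two proportions, but the only method named that yields an effect estimate works on the odds scale. With a common outcome an odds ratio is well above the ratio of uptake, and readers easily take one for the other.

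**Working it through.** **Inputs from Statistical methods.** Uptake 23% v 60%, two-sided 5%, 80% power, 10% attrition, 100 per arm. The 42% alternative, the coding of covariates and their strength are assumptions.

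**Step 1: the plan's own figure.** n per arm = [1.96√(2·0.415·0.585) + 0.84√(0.23·0.77 + 0.60·0.40)]² / 0.37² = (1.366 + 0.542)² / 0.1369 ≈ 26.6, so 27, or 30 after dividing by 0.9. With continuity correction it is 36 after attrition. Neither gives the stated 100. The counts below take 100 per arm as planned, so they do not depend on how it was derived. Power at 90 per arm is above 0.99 for the planned effect, so the issue here is the estimate, not the test.

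**Step 2: events at 90 per arm.**
- 23% v 60%: 90 × (0.23 + 0.60) = 74.7
- 23% v 42%: 90 × (0.23 + 0.42) = 58.5
- No effect: 180 × 0.23 = 41.4

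**Step 3: the model as listed.** Time to the smear exists only for women who had one. A complete-case fit would keep only those women, all with the outcome. Giving the others a single value, such as 0 or 183 days, separates the data completely. No arm effect can then be estimated. This variable, and the other two measured after randomisation, must be removed before anything else.

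**Step 4: parameters left with baseline covariates only.**
- Sparse coding: arm 1, age 1, class in three levels 2, parity linear 1, marital status in two levels 1, distance 1. Total 7.
- Fuller coding: arm 1, age 1, class in five levels 4, parity in four levels 3, marital status in four levels 3, distance 1. Total 13.

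Events per parameter: 74.7/7 = 10.7 down to 74.7/13 = 5.7 at the planned effect, and 58.5/7 = 8.4 down to 58.5/13 = 4.5 at 23% v 42%. The open list would add to the parameters.

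**Step 5: bias by simulation.** Settings: 90 per arm, about 2,000 trials per case, assumed log-odds 0.3 per covariate term. The geometric-mean fitted odds ratio is compared with its own conditional true value, so non-collapsibility is not counted as bias.
- 23% v 60%, 7 parameters: 6.28 for a true 5.67, +11%
- 23% v 60%, 13 parameters: 6.65 for a true 5.68, +17%
- 23% v 42%: +6% with 7 parameters, +10% with 13
- No effect: within 2%, about simulation error

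Repeats under similar assumptions give 9-20% at 23% v 60% and 6-11% at 23% v 42% for 7 to 13 parameters. The SD of the log odds ratio was 10-20% larger than with arm and age only. With four-level marital status and small cells assumed, about 4-24% of 13-parameter fits had a near-separated coefficient. Type I error stayed near 5-6%.

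The standardised risk difference from the same kind of model was essentially unbiased: 37.0 and 36.6 points for a true 37, and 19.0 for a true 19.

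**Step 6: what a short model saves.** With two or three one-term baseline covariates and 90-100 per arm, inflation is still about 2-6% at 23% v 60% and 2-4% at 23% v 42%. Taking 4% for the short model, the avoidable part at the planned effect is about 11 − 4 = 7 points with 7 parameters and 17 − 4 = 13 with 13. On the log scale the whole bias is ln 1.11 = 0.10 to ln 1.17 = 0.16, against an SD of 0.38-0.42, or about 0.3-0.4 of one SD.

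**Step 7: scale.**
- 23% v 60%: OR = (0.60/0.40)/(0.23/0.77) = 5.02; RR = 0.60/0.23 = 2.61; risk difference 37 points
- 23% v 42%: OR = (0.42/0.58)/(0.23/0.77) = 2.42; RR = 0.42/0.23 = 1.83; risk difference 19 points

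**The case against.** The strongest reply is that the article states neither coding nor covariate strength, so any percentage describes an assumed model. Age, parity and distance can each enter as one linear term, and coding is commonly left to a fuller document. This stands, and it is why the size is given as a range with its assumptions. The list of eight and its open end, however, are stated choices.

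Three stronger readings are tempting, and the documents support none of them.
- A reader might infer that the odds ratio is overstated across the whole span of 41 to 75 events. The 41-event case is the one with no effect, where the true odds ratio is 1 and no material inflation appears. Inflation well above 20% needs about 18 parameters, more than the baseline list requires.
- A reader might infer that the adjusted odds ratio is the protocol's declared estimate of effect. The protocol never says so, does not say that it will be read as a ratio of uptake, and also plans a chi-square or Fisher comparison. What remains true is that those are tests, and no effect measure on the proportion scale is named.
- A reader might infer that the long covariate list causes the gap between 5.0 and 2.6. It does not. That gap comes from a common outcome and appears equally in an unadjusted two-by-two table.

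It is also fair to say that the outcome-defined covariate is the worse defect in the same sentence, that the short model keeps some bias, and that the test is hardly affected. All three stand. They limit the weight of the point but do not remove it, because the inflation persists after the post-randomisation variables are taken out.

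**Conclusion.** The point holds as a cheap improvement. If the texts work, a baseline-only model of 7 to 13 parameters inflates the odds ratio by roughly 6-11% at 23% v 42% and 9-20% at 23% v 60%, with a larger SD on the log scale than a short model gives. This rests on 90 evaluable women per arm, modest assumed covariate effects and assumed coding. If the texts have no effect there is no material inflation, and type I error is essentially unaffected in either case.

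The scale point is independent of model size: at the planned effect the odds ratio is about twice the risk ratio, and the plan names no measure on the scale on which the trial was sized. Neither point makes the comparison of the arms invalid.

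**What to change.** In the analysis paragraph of Statistical methods:

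1. Take the three post-randomisation covariates out of the arm-effect model. Limit that model to arm, hospital, age and one or two further baseline variables named in advance, with their coding. Delete the open list from it.
2. Report the risk difference and risk ratio with 95% CI, obtained from this model by marginal standardisation, as the effect of the texts. Give the odds ratio as secondary.
3. Keep the longer list of baseline variables for the separate factor analysis of the secondary endpoint, with collapsed categories or penalised likelihood.

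The cost is wording only, with no extra participants or data. The team should confirm that the named software can produce the standardised estimates and their intervals, or name another package. The downside is fewer adjusted variables in the main table and a less striking figure than the odds ratio.
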